### 9.2. Populations for Analyses

The Safety population will consist of all patients who received any study medication and will be based on the treatment actually received. The Safety population will be used to present the demographic and baseline data, and all safety data.

The Intent to Treat (ITT) population will consist of all patients who are randomized and receive the IMP (either Atorvastatin or placebo); it will be based on the treatment randomized, regardless of the treatment actually received. The ITT population will be used to present efficacy data.

### 9.3. Statistical Analyses

All patient data collected on the CRF will be listed by patient and centre.

The Statistical Analysis Plan, describing details of all the statistical methods and analysis to be applied to trial results is described below. Any change in the planned analysis will be documented. The data will be presented in the clinical study report.

Continuous variables will be reported as mean  $\pm$  standard deviation (SD) if normally distributed, otherwise as median and interquartile range (IQR). For variables with right-skewed distribution, a log-transformation will be considered before analysis, otherwise nonparametric methods will be considered. Categorical variables will be presented as frequencies and percentages. All analyses will be performed using SAS version 9.4 (SAS Institute, Cary, NC, USA).

Possible differences in baseline characteristics of ACM patients belonging to the “Atorvastatin group” and the “placebo group” will be reported in a descriptive manner.

Changes in the variables of interest, measured at different timepoints, will be assessed by paired samples Student's T test or Wilcoxon signed-rank test, and will be compared between groups by Student's T test for independent samples or Mann Whitney's U test.

Differences of treatment effects on the primary and secondary endpoints in the groups will be analysed by using univariate and multivariate regression models, also taking into account possible confounding variables.

Data on the primary endpoint measures will also be available for most subjects before baseline (extended baseline). The analyses will apply time series models to compare the two groups (focusing on rate of change).

Subgroup analyses will account for other medications, underlying genetic mutations or disease stage.

As proof of mechanism, Person's or Spearman's correlation coefficients will be performed to assess possible relationships between endpoints and plasma oxLDL reduction.

Data from the psychological questionnaires will be analyzed by repeated-measures ANOVA models, in order to analyse the variables at different timepoints. For within-patient comparisons, paired sample t-tests will be implemented. Adjustments for possible confounding variables will be considered.

For the third objective, different AI models will be created to exploratively assess the association between a large number of potential predictors (below referred as variables) and the response to treatment, in terms of primary and secondary study endpoints. In this case, the test cohort will be

the “Atorvastatin Group”. Standard clinical variables and symptoms, together with biomarkers (as plasma lipids, inflammatory, cardiac damage and fibrosis markers), genotype and image-derived features (extracted from ECHO and CMR), collected at T0, will be taken into account as possible predictive variables to define the models. In particular, image-derived features will be obtained by radiomics analysis, which extracts a large number of quantitative characteristics that fail to be detected by the naked eye. Different models will be developed to describe the association of the previously described variables, either as single domains or combined, with the endpoint outcomes at T18 of the patients receiving Atorvastatin. Several feature selections (e.g. filter and wrapper methods) and AI algorithms (e.g. random forest, support vector classifier, k-nearest neighbors) will be used to develop multi-modal models for the prediction of response to Atorvastatin. In view of the relatively small sample size involved, a nested cross-validation approach will be used to overcome test set selection bias. The final model will be obtained by re-training the best performing pipeline in nested cross-validation on the entire dataset, with hyperparameter values tuned with a regular k-fold cross-validation on the whole dataset. Performance metrics will include balanced accuracy, sensitivity, specificity and f1 score.

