| Primary
Efficacy of Atorvastatin in avoiding functional RV deterioration                                                                                           | Deterioration from baseline of RV free wall longitudinal strain measured by ECHO.                                                                                                                                                                                                                                                    | Variation of strain RV free wall longitudinal strain measured by ECHO at T18 respect to T0 (%)                                                                                                                                                                                                                                                                                                                                                                                                                                                                                                                                                                                                                                                                                                                                                                                                                                                                                                                                                                                                                                                |

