-NCT05524077: “Catheter Ablation Versus Anti-arrhythmic Drugs for Ventricular Tachycardia (CAAD-VT)” to test a composite endpoint of Recurrent VT or VT storm or death following the different treatments.

Common primary endpoints are RV function or arrhythmia burden. Those trials assessing RV function use RV strain as outcome.

Accordingly, we chose the primary endpoint outcome to be a clinically relevant measurable parameter. We chose RV longitudinal strains for the following reasons:

- CCM *in vitro* results point to an action of atorvastatin in counteracting the adipogenic differentiation of cardiac cells leading to a moderation of morphological/functional remodeling of the cardiac substrate (of which strain is a measure [14]).
- CCM *in vivo* results showed a significant involvement of the right ventricle respect to the left ventricle.
- RV free wall longitudinal strain reflects the deformation of the RV in the longitudinal direction. In comparison with RV ejection fraction, it is earlier in the detection of systolic disfunction; moreover, it is linked to prognosis in many clinical conditions.
- Free wall longitudinal strain of the RV worsens over the years in ACM patients with little variability, as proven by the CCM cohort retrospective data (n=20 patients with double ECHO): 12.8% (2.4 points of strain) reduction in 18 months with a standard deviation of 4.5%.
- A similar difference of RV strain has recently been confirmed by other group publications [15],[16]. In addition, a similar standard deviation was measured in other cohorts [14].

ECHO parameters are measurable in every patient, while CMR is feasible only if the patient is not carrying an ICD or if the ICD is compatible with CMR. In the last case it suffers of some artifacts.

Secondary endpoints. Secondary endpoints will include other information regarding disease progression. Importantly, arrhythmia burden will be monitored, and it is expected to decrease, as reported for other non-ischemic populations in treatment with statins [17]. Most known clinical markers and biomarkers will be assessed, as well as the novel biomarker oxLDL [1]. In addition, it is important to evaluate safety of Atorvastatin 80 mg administration for the novel indication (ACM patients).

Exclusion criteria. They have been chosen to limit as much as possible the side effects caused by the treatment.

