## 9. Statistical Considerations

### 9.1. Sample Size Determination

A power analysis estimated that 88 patients (44 per group) will be sufficient to observe at T18 a significant ( $\alpha=0.05$ ) mean absolute difference between the two groups of 2.4 points of RV free wall longitudinal strain (%), hypothesizing a standard deviation of 4.5% and with a power of 80%. The statistical test used to calculate the sample size was an independent one-sided T test. Assuming a drop-out rate of 15% during the study, the total sample size is 102 patients (51 per group). Assuming a screening failure of about 5%, 110 patients will be screened.

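### No single primary analysis is named for RV free wall strain: Section 9.3 lists several non-equivalent between-group methods, with no baseline covariate and no stated role for the T9 ECHO

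*Protocol*

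**What the plan says.** Section 4 (repeated in the Synopsis) gives the primary measure as "Variation of strain RV free wall longitudinal strain measured by ECHO at T18 respect to T0", followed by a percent sign in brackets.

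Section 9.3 opens by stating that the Statistical Analysis Plan is set out there. It then provides, for outcomes that include the primary endpoint:

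- changes over time, which are assessed within arm "and will be compared between groups by Student's T test for independent samples or Mann Whitney's U test";
- treatment effects on the primary and secondary endpoints, analysed by "univariate and multivariate regression models, also taking into account possible confounding variables";
- for the primary endpoint measures, which most subjects will also have from before baseline: "The analyses will apply time series models to compare the two groups (focusing on rate of change").

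For sample size, Section 9.1 uses a "mean absolute difference between the two groups of 2.4 points of RV free wall longitudinal strain", and adds: "The statistical test used to calculate the sample size was an independent one-sided T test". Section 9.1.2 describes the efficacy variable as a progressive decline measured at T18.

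ECHO is scheduled at T0, T9 and T18. Section 9.3 names repeated-measures models only for the questionnaires. Section 9.1.4 uses T9 only as a cut-off: patients lost after it may have data imputed, and patients lost before it are excluded.

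**The concern.** A two-arm comparison of change, a covariate-adjusted regression and a rate-of-change model with pre-baseline data are different analyses. They give different estimates and p-values and have different power. The pre-baseline model may also rest on a different set of patients. The text does not say which one decides the trial, which covariates enter the regression, or whether the analysis is one- or two-sided.

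Two things are at stake. First, any result near 0.05 can be disputed, because another listed method may give another answer and nothing fixes the choice in advance. Second, T0 strain is measured in everyone and the T9 ECHO is collected, yet neither is given a defined use as a covariate or a repeated outcome. Precision that costs nothing may go unused in a rare-disease trial with 88 planned evaluable patients.

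**Working it through.** **Inputs from the protocol (Section 9.1).** Difference 2.4 points, SD 4.5, one-sided alpha 0.05, power 80%, 44 per arm.

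**Input not in the protocol.** The T0-T18 correlation of strain, rho. A range is used throughout.

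**1. The plan's own figure.** n per arm = 2 × (1.645 + 0.842)² × (4.5/2.4)² = 43.5, so 44. This reproduces the stated 88. The two-sided equivalent is 55.2, so 56 per arm. Noncentral-t power at 44 per arm is 79.9% one-sided and 69.6% two-sided.

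**2. Gain from adjusting for T0.** With equal variance σ² at T0 and T18, the variance of change is 2σ²(1 − rho) and the ANCOVA residual variance is σ²(1 − rho²). The ratio is (1 + rho)/2. If 4.5 is the SD of change, the ANCOVA SD is 4.5 × √((1 + rho)/2):

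| rho | ANCOVA SD | power, one-sided | power, two-sided |
|---|---|---|---|
| change score (unadjusted) | 4.50 | 80% | 70% |
| 0.4 | 3.76 | 91% | 84% |
| 0.6 | 4.02 | 87% | 79% |
| 0.8 | 4.27 | 83% | 74% |

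If 4.5 is instead the SD of a single strain value, one-sided power for ANCOVA against change score is 83% v 68% (rho 0.3), 89% v 80% (0.5), 97% v 94% (0.7) and 99% v 99% (0.8). The gain shrinks as rho rises.

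**3. How far the listed routes differ.** One-sided simulated power with SD of a value 4.5 and rho 0.5: change t-test 81%, Mann-Whitney 79%, ANCOVA 89%, slope after baseline minus slope before baseline 41%. The last is one possible reading of the time-series model, with one earlier ECHO 18 months before T0 assumed.

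**4. False positives if the route is chosen afterwards.** Null simulation: 44 per arm, SD of change 4.5, equal correlation between visits, 20,000 trials per setting, two-sided 5%. ANCOVA stands in for the regression, and the slope difference in step 3 stands in for the time-series model. Each test alone rejects in 4.8-5.2% of trials. At least one rejects in:

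| routes available | rho 0.6 | rho 0.7 | rho 0.8 |
|---|---|---|---|
| t-test, Mann-Whitney | 6.0% | 5.8% | 6.2% |
| plus ANCOVA | 7.9% | 7.3% | 7.4% |
| plus pre-baseline slope | 9.9% | 9.3% | 9.4% |

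The regression covariates and the time-series model are unspecified, so a range of about 9-11% is a fair summary. On a one-sided test the same set gives 8.7-9.3%.

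**5. Scale.** Section 5.5 reports "12.8% (2.4 points of strain) reduction in 18 months with a standard deviation of 4.5"%. The two figures together imply a baseline of 2.4/0.128 = 18.75 points. An SD of 4.5% relative to that baseline would be 0.045 × 18.75 = 0.84 points. The sample size treats 4.5 as points, alongside a difference in points.

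**The case against.** The best defence is that the intended test can be guessed. Section 9.1 sizes the trial on an independent t-test at T18. The t-test and Mann-Whitney are joined by an *or*, with a general remark on normality in the same section, so they form one alternative pair. Choosing between them by a normality test keeps the error rate at about 5.2-5.5% in simulation. A change score already uses T0 by subtraction, and the wording on confounders and timepoints leaves room for T0 and T9. All of this stands, but it only hints. Section 9.3 never says that the sizing test is the primary analysis, and it applies regression and time-series models to the same endpoint on an equal footing.

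Comparing group A with group B under blinded labels does not help. It hides which arm is which, not which method separates them.

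Four stronger readings are tempting and not supported:

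- **That the endpoint is defined on two contradictory scales.** Strain is itself measured in percent, other brackets in the same table mostly give units, and Section 9.1 sizes on absolute points. This is an ambiguity to clear up, not a contradiction.
- **That the error rate reaches 15% or more.** That requires adding a percent-change analysis and a T18-only comparison, which Section 9.3 does not list.
- **That power starts from 70%.** That is the two-sided figure, and the protocol sizes one-sided.
- **That an unadjusted comparison of change is the weakest choice.** In step 3 it beats Mann-Whitney and, by a wide margin, the pre-baseline slope. Baseline adjustment is the more efficient method, but leaving it out is not an error.

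**Conclusion.** The point holds. In the section that the protocol presents as its analysis plan, the primary endpoint has several non-equivalent between-group analyses and none is designated primary. No baseline covariate is named, and the T9 ECHO has no stated role.

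The 9-11% false-positive rate applies only if the result is chosen after the data are seen. It rests on an assumed correlation of 0.6-0.8 and on one reading of the unspecified models. The protocol does not say that such a choice will be made, but nothing in it rules the choice out.

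The power gain from T0 adjustment is 80% to about 83-91% one-sided, or 70% to about 74-84% two-sided, for a correlation of 0.8 down to 0.4. It assumes that 4.5 is the SD of change, which the protocol does not state.

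**What to change.** Amend Sections 4 and 9.3 before unblinding:

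- Name one primary analysis of RV free wall strain in absolute points at T18. It can be ANCOVA with T0 strain as covariate. It can instead be a mixed model with T9 and T18 as outcomes and T0 strain, arm, visit and arm-by-visit as terms. T0 must not also be an outcome in that model. The two are not interchangeable once T18 values are missing, so choose one.
- Report the T18 difference between arms with its confidence interval and p-value, and state the sidedness.
- State that the percent sign in the endpoint table is the unit of strain, not relative change, and say what quantity the SD of 4.5 describes.
- Label the Mann-Whitney, multivariable and extended-baseline models as sensitivity or supportive analyses.

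The cost is wording only. The T0, T9 and T18 ECHOs are already scheduled, and no new data or patients are needed.

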#### 3.1. Study Rationale

The present SEARCH TRIAL relies on solid preliminary *in vitro* and *in vivo* data suggesting novel pharmacologically targetable ACM pathogenic mechanisms. Retrospective studies in ACM patients of Centro Cardiologico Monzino IRCCS showed that oxidized low density lipoproteins (oxLDL) plasma levels were associated with severe ACM phenotypes, as increased cardiac lipid accumulation, cardiac dysfunction, and arrhythmic burden. Preclinical studies in an ACM mouse showed that Atorvastatin treatment reduced oxLDL levels and prevented ACM phenotype development [1]. Based on findings of the Centro Cardiologico Monzino IRCCS, we propose that the use of statins in patients suffering from ACM may have beneficial effects in reducing the progression of the pathology and avoiding the most severe consequences of the disease. Indeed, beyond the described canonical lipid-lowering effects, atorvastatin has known pleiotropic effects, as anti-oxidant, anti-inflammatory and anti-arrhythmic, leading, in ACM patients, to lowering of the triggering factor oxLDL, reduction of the inflammatory mediated disease bursts, and moderation of the arrhythmia burden.

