## **5.6. Justification for Dose**

The dose of the drug has been selected after an in-depth evaluation of the literature. Previous clinical trial demonstrated the efficacy of 80 mg/die orally atorvastatin to reduce oxLDL plasma concentrations, modulate oxidative stress and inflammation, as desirable in ACM patients [20,21]. The same dose is demonstrated to be safe and with a similar incidence of adverse effects if compared to lower doses [22,23]. In addition, the median duration of 80 mg atorvastatin treatment in previous clinical trials is 22,56 months, indicating the safety of the treatment for 18 months as proposed in our trial.

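### The oxLDL correlation planned as proof of mechanism has no term for randomised arm; if the arms are analysed together, it can reach significance too often when oxLDL plays no role

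*Protocol*

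**What the plan says.** Section 9.3 of the protocol states: "As proof of mechanism, Person's or Spearman's correlation coefficients will be performed". The sentence gives the purpose and the quantities to be correlated: "correlation coefficients will be performed to assess possible relationships between endpoints and plasma oxLDL reduction". No arm, timepoint or covariate is named.

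The same section presents its text as the statistical analysis plan, "describing details of all the statistical methods and analysis to be applied to trial results is described below", so on the protocol's own account this is the specification of the method.

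Section 9.3 mentions confounders in two other places. One is the comparison of treatment effects ("Differences of treatment effects on the primary and secondary endpoints in the groups will be analysed by using univariate and multivariate regression models"); the other is the questionnaire analysis. Neither covers the oxLDL correlation. Section 9.2 assigns efficacy data to the ITT population, which contains both arms.

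The treatment is expected to move oxLDL. Section 5.6 says: "Previous clinical trial demonstrated the efficacy of 80 mg/die orally atorvastatin to reduce oxLDL plasma concentrations". Section 3.1 counts "lowering of the triggering factor oxLDL" among the expected consequences, but lists it beside other actions: "atorvastatin has known pleiotropic effects, as anti-oxidant, anti-inflammatory and anti-arrhythmic".

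**The concern.** A Pearson or Spearman coefficient does not know which arm a patient is in. In a combined sample, anything that shifts both variables by arm appears as correlation. The trial assumes such a shift: atorvastatin is expected to lower oxLDL and to slow the loss of RV strain. If the strain benefit came through reduced inflammation, treated patients would still have both larger oxLDL falls and better strain, and the coefficient would be positive on average with no connection between the two in any patient.

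What is at stake is the interpretation of a positive trial. oxLDL is the scientific premise of the study (sections 3.1 and 3.2), so a significant correlation is likely to be quoted in support of it. A coefficient without an arm term cannot separate the oxLDL route from the other routes that the protocol names, which is the purpose its label gives it.

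**Working it through.** **Inputs from the protocol.** Section 9.1: strain difference 2.4 points, SD 4.5, alpha 0.05 one-sided, power 80%, 44 evaluable patients per group. Section 7.3: 1:1 allocation.

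**Input not in the protocol.** The size of the oxLDL reduction. I assumed 0.5 to 3 within-arm SD.

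**Step 1: reproduce the planned sample size.** n per arm = 2 × (1.645 + 0.842)² × (4.5/2.4)² = 2 × 6.185 × 3.516 = 43.5, so 44. This agrees with section 9.1. The standardised strain effect is d1 = 2.4/4.5 = 0.533.

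**Step 2: correlation created by arm alone.** Let d2 be the standardised treatment effect on oxLDL reduction. With 1:1 arms and zero correlation within each arm, the covariance across all patients is 0.25·d1·d2, and the variances are 1 + 0.25·d1² and 1 + 0.25·d2². Hence

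r = 0.25·d1·d2 / √[(1 + 0.25·d1²)(1 + 0.25·d2²)].

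For d2 = 1: 0.1333 / √(1.0711 × 1.25) = 0.115. As d2 grows without limit, r tends to 0.5·d1 / √(1 + 0.25·d1²) = 0.2667 / 1.0349 = 0.258.

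**Step 3: how often this is significant.** With 88 patients, two-sided significance at 0.05 needs |r| above 1.988 / √(86 + 1.988²) = 0.21. I simulated 20,000 trials per setting, with 44 per arm, normal outcomes and no within-arm association. The last column uses a partial correlation given arm.

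| Assumed oxLDL shift (SD) | r from formula | Both arms together, significant | Same, among trials with a positive primary test | Adjusted for arm, significant |
|---|---|---|---|---|
| 0.5 | 0.06 | 9% | 10% | about 5% |
| 1 | 0.12 | 19% | 22% | about 5% |
| 1.6 | 0.16 | 33% | 39% | about 5% |
| 2 | 0.18 | 41% | 49% | about 5% |
| 3 | 0.21 | 53% | 66% | about 5% |

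Spearman coefficients give similar rates (8%, 19%, 43% and 53% at 0.5, 1, 2 and 3 SD). Correlation within the atorvastatin arm alone also stays at about 5%. If treatment moves only one of the two variables (d1 = 0 or d2 = 0), the combined-arm rate returns to about 5%.

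**Step 4: what arm adjustment costs if the hypothesis is true.** Suppose that oxLDL carries the whole strain effect, so the within-arm correlation is d1/d2 (0.33 at 1.6 SD, 0.18 at 3 SD). The power to detect the correlation is then:

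| oxLDL shift (SD) | Both arms together | Adjusted for arm | Atorvastatin arm only |
|---|---|---|---|
| 1.6 | 98% | 89% | 62% |
| 3 | 85% | 38% | 21% |

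**The case against.** The strongest objection is that the protocol never says that the arms are combined. A reader might infer that pooling is the plan, but the document is silent. A fall in oxLDL can be read as something that happens in treated patients, and the response-prediction work in section 9.3 uses the atorvastatin group alone. A within-arm correlation carries no artefact. This stands, and the point is therefore conditional. It does not dispose of the matter: section 9.3 presents itself as the full analysis plan, section 9.2 uses both arms for efficacy data, and the protocol names a single cohort where it wants one.

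A reader might also infer that a positive trial would deliver the mechanism result automatically. The figures do not support that. At the planned strain effect the average spurious coefficient never exceeds about 0.26. Even among trials with a positive primary test, fewer than half give a significant correlation until the assumed oxLDL shift is above about 2 SD. The error rate is inflated; a false result is not assured.

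Nor is adjustment free. Under full mediation the between-arm difference is real signal, and removing it costs most power where the artefact is largest (step 4). That does not rescue the combined coefficient, because the between-arm part is the part that cannot tell the routes apart.

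Finally, the correlation is not listed among the objectives in section 4 and has no decision rule. The sentence itself speaks only of possible relationships; it is the lead-in label that claims too much. The anti-arrhythmic route may bear little on strain, since section 5.5 regards the effect on arrhythmia as indirect. The anti-inflammatory route is enough for the argument. These points limit the weight of the finding but do not remove it.

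**Conclusion.** The point holds in conditional form. As written, the analysis has no arm term and no restriction to one arm. If it is run on both arms together, and atorvastatin lowers oxLDL while affecting the endpoint by another route, the chance of a significant correlation with no within-arm link is about 9% to 53%, against a nominal 5%.

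This rests on the planned strain effect of 0.53 SD, 44 patients per arm, normal outcomes, a two-sided 0.05 test of the coefficient, and assumed oxLDL shifts of 0.5 to 3 SD. The artefact disappears if treatment moves only one of the variables or if the correlation is done within arm. The primary comparison is untouched.

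This is a cheap improvement to a supportive analysis, not a defect in the trial's main inference.

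**What to change.** In section 9.3, specify a partial correlation (Pearson or Spearman) between the change in the endpoint and the reduction in oxLDL, adjusted for randomised arm, and show the coefficient within each arm beside it. Adjustment for baseline oxLDL and the baseline value of the endpoint is optional. Call the result an exploratory association: even within an arm the correlation is observational (adherence, for example, could drive both changes) and would not prove a mechanism.

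State in the same place that a null adjusted correlation does not refute the oxLDL hypothesis, given the power loss in step 4. The coefficient from both arms together may be shown as a description only.

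The cost is a sentence or two and one model term. No new data are needed, because blood for the ACM biomarkers (oxLDL among them) and ECHO are already scheduled at T0, T9 and T18. The real price is lower power if oxLDL does mediate the effect.
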